#### Data Collection for Participants With ADHD

Initially, participants with potential ADHD will be recruited via public call using convenience sampling. Announcements will be shared through the researchers’ and partner institutions’ (universities and preparatory schools for college entrance exams in the city of Porto Alegre, capital of the southernmost state of Brazil) social media channels.

Interested individuals will contact the staff through social media platforms, email, or other instant messaging apps and will receive a REDCap survey link containing an informed consent form and the following instruments: sociodemographic survey, LSAS, BDEFS, Weiss Functional Impairment Rating Scale–Self-Report, and ASRS-18. Following the screening, participants who report 5 or more symptoms in the ASRS-18 will undergo psychiatric and neuropsychological assessments. Those who meet the inclusion criteria for the ADHD group will take the standardized exam.

#### Data Collection for Controls

Due to logistical constraints related to team resources, the sequence of procedures for the control group will differ from that used for the ADHD group. We will partner with colleges and preparatory schools to present the research protocol during regular classes. Interested individuals who report no prior ADHD diagnosis will be invited to participate in the on-site intervention on a predetermined date. Sessions will be held in the exact same manner as done with participants with ADHD. Immediately before the test session, potential control group students will complete a printed version of the ASRS-18. On the basis of these results, students exhibiting less than 4 symptoms on the scale will be invited to participate in the subsequent stages of the study (REDCap surveys, psychiatric assessment, and neuropsychological testing).

#### Intervention Procedures

To minimize fatigue, the intervention will be administered on a separate day from the psychiatric and neuropsychological assessments in groups of 5 to 15 participants and will always be administered in the morning. To assess participants’ optimal performance, they will be instructed to take medications as usual. Information regarding dose and time of intake will be collected on the day of the intervention. Each session will be facilitated by at least one assistant and the principal investigator (PI). Sessions will be conducted in quiet university or preparatory school classrooms to maintain a naturalistic environment.

Each participant will complete an academic exam with 3 different versions (A, B, and C) of similar difficulty and length. Each version will be paired with 1 of 3 distinct time conditions: 40 minutes (standard), 50 minutes (25% extra time), and 60 minutes (50% extra time). To control for potential confounding variables and ensure that the results are not biased by the order of conditions or exam versions, both the sequence of the exam versions and the time conditions will be randomized for each participant, as illustrated in Figure 1. This counterbalanced design ensures that each participant experiences all 3 time conditions (40, 50, and 60 minutes) and each exam version (A, B, and C) in a different order, preventing any systematic influence from order effects on the outcomes. Sequences of task orders will be computer generated using a random number generator and then counterbalanced so that each condition appears equally often in each position across participants.

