### Procedures

#### Overview

Data will be collected and managed using REDCap (Research Electronic Data Capture; Vanderbilt University), a secure, web-based software designed to support data capture for research studies [48]. The intervention will be conducted at Universidade Federal do Rio Grande do Sul, the neuropsychological assessments will be conducted at Hospital de Clínicas de Porto Alegre’s Clinical Research Center, and the psychiatric assessments will take place online using a secure web-based videoconferencing platform. To enhance recruitment efficiency, we will adopt 2 different strategies for students with ADHD and controls.

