### Statistical Analysis

Primary performance analyses will use standardized, IRT‑equated scores from the ENEM‑based exams; raw counts will not be analyzed. Estimated marginal means with 95% CIs will summarize group profiles and within‑person gains. We will also conduct a sensitivity analysis excluding medicated individuals.

Group comparisons at each time limit (40, 50, and 60 minutes) will be performed using Welch *t* tests with Cohen *d* and 95% CIs. Within‑group time effects will be evaluated via repeated‑measure ANOVA with time (40, 50, and 60 minutes) as a within‑subject factor; the Mauchly test will assess sphericity, and Greenhouse-Geisser corrections will be applied when necessary. Planned paired contrasts (50 vs 40 and 60 vs 40 minutes) will use Bonferroni adjustment, and partial η^2^ will index omnibus within‑subject effects.

To directly test whether extended time benefits participants with ADHD more than controls, we will fit a linear mixed‑effects model with a random intercept for participant, coding time continuously in minutes (40, 50, and 60) so slopes are interpretable per minute. Fixed effects will use Satterthwaite df, and interaction tests will be corroborated with likelihood ratio comparisons under maximum likelihood.

Assumptions will be examined using Shapiro-Wilk tests and *Q*-*Q* plots (normality), Levene tests (homogeneity), and visual inspection of mixed‑model residuals. When ANOVA assumptions are not met, inference will prioritize mixed‑model results. Analyses will be conducted in R (*lme4* and *lmerTest*, *emmeans*, and *afex* packages; R Foundation for Statistical Computing).

Missing data will be handled using multiple imputation under the assumption that data are missing at random, and all analyses will be conducted on the imputed datasets using an intention‑to‑treat approach.

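### Exams are sat in group sessions, but the between-group comparisons at 40, 50 and 60 minutes carry no session term, so their standard errors may be too small and session or venue differences can pass as group differences

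*Protocol article*

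**What the plan says.** **Sessions.** Under Intervention Procedures the exam is given "in groups of 5 to 15 participants and will always be administered in the morning". Each session has the principal investigator and at least one assistant, a shared briefing, and time kept on a whiteboard.

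**Venue.** The Overview under Procedures says "The intervention will be conducted at Universidade Federal do Rio Grande do Sul". Intervention Procedures says "Sessions will be conducted in quiet university or preparatory school classrooms to maintain a naturalistic environment". Data Monitoring and Oversight describes the study as single-center.

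**Routes to the exam.** Controls are approached in regular classes at partner colleges and preparatory schools. They "will be invited to participate in the on-site intervention on a predetermined date", and their psychiatric and neuropsychological assessments come afterwards. ADHD participants answer a public call and are assessed first: "Those who meet the inclusion criteria for the ADHD group will take the standardized exam". Of the control sessions the article says: "Sessions will be held in the exact same manner as done with participants with ADHD".

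**Order.** Within a session, "both the sequence of the exam versions and the time conditions will be randomized for each participant".

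**Analysis.** Statistical Analysis plans Welch t tests between groups at each of the three time limits, with Cohen d and 95% CIs. It also plans repeated-measures ANOVA and paired contrasts within each group, and a linear mixed model "with a random intercept for participant". No session or venue term is named.

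**The concern.** People tested together share a room, a date, a briefing and a clock, and controls recruited from one class may also share teaching. Their scores may therefore be more alike than those of people tested on different days. A Welch test counts each of them as an independent observation.

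If ADHD and control participants are also tested in different sessions, session is nested in group. Session-to-session variation then adds to the variance of the group difference without entering its standard error. A systematic difference between the rooms, dates or venues used for the two groups would appear as a group difference.

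At stake are the three group comparisons and the group main effect in the mixed model. They will be reported with effect sizes and intervals, and are easily read as the size of an ADHD deficit at each time limit.

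**Working it through.** **Inputs from the article.** Session size m = 5 to 15 (Intervention Procedures). Planned 40 per group, d = 0.45, 80% power, P of .05 (Sample Size Calculation). Enrolled 43 controls and 60 ADHD participants, 103 in all (Results, Overview).

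**Assumptions.** The session intraclass correlation (ICC) is not given; 0.02, 0.05 and 0.10 are shown. Each session is taken to hold one group only. Tests are two-sided.

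**1. The plan's own sample size.** For a paired test within each group, n = ((1.960 + 0.842)/0.45)² = 38.8, so 39 per group and 78 in total. The exact paired t test needs 41 per group (82 in total) and has 79.3% power at 40. The stated 80 therefore reproduces as a within-subject figure with no allowance for clustering. It was not sized for the between-group tests: a two-sample test at d = 0.45 would need 78 per group (156 in total), and 40 per group gives 52% power.

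**2. Number of sessions.** 103/15 = 6.9 and 103/5 = 20.6, so roughly 7 to 21 sessions.

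**3. Between-group comparison at one time limit.** Design effect DE = 1 + (m − 1) × ICC. True two-sided error of a nominal 5% test = 2 × (1 − Φ(1.96/√DE)). Example with m = 10 and ICC = 0.05: DE = 1 + 9 × 0.05 = 1.45, √DE = 1.204, 1.96/1.204 = 1.628, error 10.4%.

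| m | ICC 0.02 | ICC 0.05 | ICC 0.10 |
|---|---|---|---|
| 5 | DE 1.08, 5.9% | DE 1.20, 7.4% | DE 1.40, 9.8% |
| 10 | DE 1.18, 7.1% | DE 1.45, 10.4% | DE 1.90, 15.5% |
| 15 | DE 1.28, 8.3% | DE 1.70, 13.3% | DE 2.40, 20.6% |

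The standard error is understated by a factor of √1.08 = 1.04 to √2.40 = 1.55. The planned 80 participants carry the information of 80/1.08 = 74 down to 80/2.40 = 33.

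**4. Within-person comparisons.** Write a score as Y = μ(group, time) + session effect + participant effect + residual. Each participant sits all three limits in one session. In the 60 minus 40 difference the session effect (including venue) and the participant effect both cancel. What is left is the group's mean gain plus residual error.

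**5. Simulation of both** (20,000 runs, 40 per group, sessions nested in group, within-person correlation assumed 0.6).
- Additive session effects, ICC 0.05 and 0.10. Welch test: 7.5% and 10.1% (m = 5), 10.5% and 15.9% (m = 10), in line with the formula. Group-by-time test and within-group 60 vs 40 contrast: 4.7% to 5.3% throughout.
- Session also changes the gain, explaining 5% of gain-score variance (assumed). Group-by-time test and within-group contrast: about 7% to 8% (m = 5) and 10% to 11% (m = 10).

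**The case against.** The strongest objection is that the analysis built to test the main hypothesis is not the one at risk. The article's direct test of greater benefit in ADHD compares time slopes between groups, and additive session and venue effects drop out of it. That stands. A reader might infer from the missing session term that the group-by-time result is invalid, but the design does not support this. Inflation there needs session to alter the gain from extra time. That is conceivable, because people in one room work to different limits and change exams at different moments, but nothing in the article shows that it happens.

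Second, a reader might take separate sessions as a stated fact. They are an inference from the two recruitment routes and from the wording on control sessions. If sessions were mixed, the inflation in step 3 would not follow.

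Third, 5 to 15 is the number in the room, not the number analysed. Controls sit the exam before eligibility is settled. If those later excluded leave the analysis, the clusters shrink. At ICC 0.05, going from 10 to 5 per session lowers the error rate from 10.4% to 7.4%.

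Fourth, the ICC is assumed, and several features limit session variation: the principal investigator attends every session, all are held in the morning, and limits and start times are fixed. This argues for the lower part of the range but does not bring the ICC to zero.

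Finally, an article condenses its analysis plan. Here, though, it names both the between-group test and the random structure, and what it names omits the clustering that its own procedures create.

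**Conclusion.** The point holds for the between-group comparisons only: the Welch tests at 40, 50 and 60 minutes and the group main effect in the mixed model. With any positive within-session correlation and sessions largely of one group, their standard errors are too small. The true error rate is about 6% to 21% over the session sizes in the article and an assumed ICC of 0.02 to 0.10, and less if sessions are mixed or the analysed clusters are smaller. Session or venue differences can also pass as group differences in these comparisons; the article does not show that they do.

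The within-group time contrasts and the group-by-time test stay near 5% under additive session or venue effects. They are at risk only if session modifies the gain.

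Separately, the two statements on venue do not agree.

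**What to change.** - **Main change.** Add a random intercept for session to the mixed model and take the group comparisons at each time limit from it instead of from Welch tests. Entering time as a factor for this purpose avoids forcing the three differences onto a straight line.
- **Sensitivity analyses.** Add a session-by-time term if it can be estimated, and repeat the group-by-time test using university-held sessions only.
- **Stated limitation.** Say whether sessions held one group or both. If sessions are nested in group, say that no model term can remove session or venue confounding of the group main effect; a random intercept corrects only the standard errors.
- **Text.** Reconcile the Overview under Procedures with Intervention Procedures on where sessions take place.

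Changing how sessions are scheduled is not proposed: 103 people are enrolled against 80 planned, and analysis began in March 2026.

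**Cost.** One random term and two sensitivity analyses, using session date and room. Intervals will be slightly wider. With about 7 to 21 sessions, the session variance may be estimated near zero and the session-by-time term may not be estimable. The model also assumes a common residual variance, which the Welch test does not, so this should be checked in the residuals.

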**Figure 1 figure1:**
[figure not shown]
Sequence of the exam versions and time conditions randomized for each participant.

At the beginning of each session, the PI will explain the procedure to the participants. The designated time limits will be informed on the first page of the exams. When the time limit of the exam is reached, participants will be stopped and handed the next exam. Only answers marked on a separate answer sheet will be considered. The time will be tracked on a whiteboard. Participants will be instructed to remain until the end of each exam regardless of finishing before the allocated time to minimize the risk of rushing through the test. Participants will start each exam at the designated beginning time.

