**Figure 2 figure2:**
[figure not shown]
Participant flow. Allocation was randomized across exam order (6 possible sequences; eg, ABC, ACB, BAC, BCA, CAB, and CBA) and time allocation order (6 possible sequences; sequence 1 [S1]=40-50-60; sequence 2 [S2]=40-60-50; sequence 3 [S3]=50-40-60; sequence 4 [S4]=50-60-40; sequence 5 [S5]=60-40-50; sequence 6 [S6]=60-50-40). The final distribution included both the attention-deficit/hyperactivity disorder (ADHD) and control groups.

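### Counterbalancing balances position but not prior testing time: the 60-minute exam starts on average 10 minutes earlier into testing than the 40-minute exam, a small possible bias the plan says is prevented

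*Protocol article*

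**What the plan says.** Under Intervention Procedures, each participant sits three exam versions under three limits: 40, 50 and 60 minutes. Task orders are randomized and then "counterbalanced so that each condition appears equally often in each position across participants". The stated result is that the design is "preventing any systematic influence from order effects on the outcomes". The Figure 2 legend lists the time orders: "sequence 1 [S1]=40-50-60; sequence 2 [S2]=40-60-50; sequence 3 [S3]=50-40-60; sequence 4 [S4]=50-60-40; sequence 5 [S5]=60-40-50; sequence 6 [S6]=60-50-40".

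On the session itself, the text after Figure 1 says: "When the time limit of the exam is reached, participants will be stopped and handed the next exam". Early finishers wait: "Participants will be instructed to remain until the end of each exam regardless of finishing before the allocated time". It adds: "Participants will start each exam at the designated beginning time". No break between exams is described.

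Statistical Analysis fits a linear mixed model with time in minutes and a participant random intercept. It names no term for position or prior testing. Under Pilot Study, Table 1 reports no significant order effect in 30 students.

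**The concern.** In most crossover designs, placing each condition equally often in each position also equalises what came before it. Here it does not, because the condition is a length of time. A participant who reaches the 60-minute exam has sat only the shorter exams. One who reaches the 40-minute exam has sat only the longer ones.

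If performance falls with elapsed minutes, the 60-minute exam begins from a fresher state. The difference would be credited to extra time. The gap runs in the direction of the trial's hypothesis, does not shrink with sample size, and lies along the same axis as the slope the mixed model estimates. The authors themselves treat fatigue as a threat: assessments are moved to another day for that reason.

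**Working it through.** **Inputs.** Durations of 40, 50 and 60 minutes and hand-over at the limit (Intervention Procedures); six time orders (Figure 2 legend); pilot order 1 versus 3, t = −0.19 on 29 df (Table 1); d = 0.45 (Sample Size Calculation). Equal use of the six orders is taken from the counterbalancing statement.

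**1. What the plan claims about position.** Over the six orders, each condition falls twice in each of the three positions, with mean position 2.0. This part is correct.

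**2. Minutes of testing before each exam.** Summing the earlier exams in each order:

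| Condition | Position 1 | Position 2 (mean) | Position 3 | Overall mean |
|---|---|---|---|---|
| 40 min | 0 | (50+60)/2 = 55 | 110 | 55 |
| 50 min | 0 | (40+60)/2 = 50 | 100 | 50 |
| 60 min | 0 | (40+50)/2 = 45 | 90 | 45 |

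The closed form is (150 − T)/2, where T is the condition in minutes. Each extra minute allowed goes with 0.5 minute less prior testing, so 60 versus 40 differs by 10 minutes. Regressing prior minutes on condition with participant effects gives −10 for 60 versus 40, both with and without position terms. The imbalance sits within positions 2 and 3, which is why a position factor cannot absorb it.

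**3. Size of bias under linear decline.** Bias in the 60 minus 40 contrast = decline per minute × 10.

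The pilot bounds the decline. For order 1 versus 3, the standardized paired difference is −0.19/√30 = −0.03, and the 95% half-width is 2.045/√30 = 0.37, giving about −0.41 to 0.34. The article does not state the direction of subtraction, so both limits are used. It does not state the pilot's time limits either. I assume 100 minutes between the starts of positions 1 and 3, which is the mean of 110, 100 and 90.

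- Decline limit: 0.34 × 60/100 = 0.20 to 0.41 × 60/100 = 0.24 SD of paired differences per hour.
- Bias limit: 0.34 × 10/100 = 0.034 to 0.41 × 10/100 = 0.041.
- As a share of d = 0.45, if read in the same unit: 0.034/0.45 = 8% to 0.041/0.45 = 9%.
- If all pilot exams lasted 40 minutes (80-minute spacing): 0.34 × 10/80 = 0.04 to 0.41 × 10/80 = 0.05.

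**4. Cost of adjusting for prior minutes.** With unit residual variance and one set of six orders, the standard error of the time slope is 1/√(6 × 200) = 0.02887. With prior minutes added it is 0.02901, a rise of 0.5%. With prior minutes and a position factor together it is 0.0577, which is double.

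**5. What that adjustment does if order effects follow position.** Take a pure practice gain of 0.1 SD per exam, no fatigue and no time effect. The planned model gives 0.000 for 60 minus 40. The model with prior minutes reads the gain as about 0.002 SD per prior minute and returns 0.002 × 10 = +0.02, a spurious benefit.

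**The case against.** **The direction is not certain.** Every version has 12 questions, so prior items are balanced exactly: 0, 12 or 24 by position, mean 12 per condition. Part of the extra prior time may be idle waiting. The 60-minute exam also follows the two more time-pressured exams. If fatigue follows items or pressure rather than minutes, the bias could be nil or reversed. This stands, and makes the direction conditional.

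**Midpoints are equal.** Mean elapsed time at mid-exam is 55 + 20 = 50 + 25 = 45 + 30 = 75 minutes in all three conditions. If decline is linear and answering is spread evenly over the allotted time, the net effect on the contrast is zero. The counter-view is that tiring during the extra minutes belongs to the condition, whereas a fresher start does not. Both readings are defensible, so the bias formula depends on which is meant.

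**Start times may be common slots.** Clock time would then be equal, but prior testing would still average 55, 50 and 45 minutes, with longer idle time after the shorter exams. The imbalance in prior testing remains.

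**Stronger readings a reader might infer.** One is a bias of 0.05 to 0.10 SD, from assumed declines of 0.3 to 0.6 SD per hour. At 100 minutes' spacing the pilot limits lie below that range in units of paired differences. In raw-score SD, 0.3 would need a between-exam correlation of at most 0.25 (0.245 × √(2 × 0.75) = 0.30), and 0.6 is out of reach at any correlation of zero or more (0.245 × √2 = 0.35). Another is that the ADHD-specific benefit is biased. That requires a faster decline per minute in the ADHD group. No figure in the article supports one, and no group split is reported for the pilot.

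**Conclusion.** The concern holds in limited form. The 55/50/45 imbalance follows exactly from the listed orders and the hand-over rule, and the statement that systematic order influence is prevented describes a property the design lacks. Position and prior items are balanced; prior testing time is not.

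The consequence is small. An upward bias in the 60 versus 40 contrast and in the time slope arises if performance falls with elapsed minutes and the starting state is what counts. It is then probably no more than about 0.03 to 0.04 SD of paired differences. That bound rests on linear decline, on the pilot interval and on the assumed 100-minute spacing; 80 minutes would raise it to about 0.04 to 0.05. The group-by-time interaction is affected only by a difference in decline between groups, whose size is unknown. The omission of a period term from a condensed article is not itself an error. The error is the claim.

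**What to change.** 1. Replace the sentence in Intervention Procedures with one saying that ordinal position is balanced across conditions but prior testing time is not (means 55, 50 and 45 minutes).

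2. Keep the planned mixed model as the main analysis. Beside it, specify a sensitivity analysis that adds scheduled testing minutes completed before each exam, taken from the allocation list, and their interaction with group, without a position factor. The article says data analysis began in March 2026, so the date of this addition should be recorded.

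The cost is one covariate and one interaction; the elapsed-minutes term raises the standard error of the time slope by about 0.5%. The downside should be stated with the results. This model assumes that order effects follow minutes. If they follow position, as practice would, it adds about +0.02 SD to 60 minus 40 for a gain of 0.1 SD per exam. For that reason it should not replace the planned model.

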### Participant Flow

A total of 1169 individuals were initially assessed for eligibility. Of these 1169 individuals, 871 (74.5%) were excluded during the online screening phase due to duplicate entries (n=9, 1%), failure to complete the screening questionnaire (n=651, 74.7%), or not meeting the inclusion criteria (n=211, 24.2%). The remaining 298 participants were invited for a psychiatric and neuropsychological assessment, after which an additional 120 (40.3%) individuals were excluded. Reasons for exclusion at this stage included failure to respond to scheduling attempts (47/120, 39.2%) or not attending the assessment (12/120, 10%), as well as not meeting the clinical or demographic inclusion criteria (55/120, 45.8%), such as having insufficient symptom severity (20/55, 36.4%), mood disorders (20/55, 36.4%), autism spectrum disorder (2/55, 3.6%), psychotic symptoms (2/55, 3.6%), or visual impairment (1/55, 1.8%); being older than 40 years (3/55, 5.5%); or having an educational level above the eligible range (5/55, 9.1%) or an IQ below 80 (2/55, 3.6%). IQ was assessed through a neuropsychological assessment as described previously. Additionally, 5% (6/120) of the participants at this stage withdrew from the study. A total of 178 participants were subsequently assigned to the intervention; however, 75 (42.1%) did not attend the intervention sessions (Figure 2).

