### Pilot Study

No significant differences were found among the 3 task versions or across administration orders (Table 1).

**Table 1 table1:** Test type and order comparisons.

Comparison		Statistical test		Statistic		*P* value	Adjusted *P* value

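### Exam position and exam version are randomised design factors, but no planned performance analysis names them; the likely cost is precision, not bias

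*Protocol article*

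**What the plan says.** All references are to the protocol article.

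- **Design.** Under Intervention Procedures, "both the sequence of the exam versions and the time conditions will be randomized for each participant". The Figure 2 caption gives six exam orders and six time orders, so 6 × 6 = 36 combinations. Sequences are then "counterbalanced so that each condition appears equally often in each position across participants". The section does not say whether this holds separately within ADHD and control.
- **Claim.** The same section credits the counterbalanced design with "preventing any systematic influence from order effects on the outcomes".
- **Analysis.** Statistical Analysis specifies Welch tests at each time limit, a within-group repeated-measures ANOVA with time as its factor, paired contrasts (50 vs 40 and 60 vs 40 minutes), and a mixed model "with a random intercept for participant, coding time continuously in minutes". None mentions position or version. The scores analysed are IRT-equated.
- **Attendance.** Participant Flow reports that of 178 assigned, "75 (42.1%) did not attend the intervention sessions". Results gives 60 ADHD and 43 control participants.
- **Pilot.** For 30 students: "No significant differences were found among the 3 task versions or across administration orders".

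**The concern.** Each participant sits three exams, allowed 40 + 50 + 60 = 150 minutes in total, in one morning session. Every score therefore carries a time condition, a position and a version. Counterbalancing makes position and version independent of time on average. It does not remove the variance they contribute, and it does not guarantee balance in the sample that attends. IRT equating may deal with version difficulty, but it does nothing about practice or fatigue across positions.

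The comparison most exposed is group by time, which is the differential-benefit question. It is a between-group difference in within-person change, so chance differences between groups in how time conditions fall over positions feed straight into it. Under the scenarios below its power is only about 50 to 61% without the extra terms, so recoverable precision is worth having.

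**Working it through.** **1. The article's own figures.** 75/178 = 42.1%, as stated. 178 − 75 = 103 = 60 + 43. Since 103 = 3 × 34 + 1 and 43 = 3 × 14 + 1, a condition cannot appear equally often in three positions overall or among controls. It could among the 60 with ADHD (3 × 20).

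**2. Chance imbalance if sequences were pooled across groups.** In a simulation with sequences balanced over 178 and 103 attending at random, the group difference in mean position (60-minute minus 40-minute exam) has SD 0.28 positions and exceeds 0.56 positions in 5% of draws. A linear first-to-last shift of *s* residual SD is *s*/2 per position. An imbalance of 0.56 then gives, in that one sample, a spurious differential gain of:
- *s* = 0.3: 0.56 × 0.15 = 0.08 SD
- *s* = 0.5: 0.56 × 0.25 = 0.14 SD
- *s* = 1.0: 0.56 × 0.50 = 0.28 SD

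Over randomisations these average to zero.

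**3. Effect on variance (pooled case).** With residual SD 1, the group difference in 60-minus-40 change has variance 2 × (1/60 + 1/43) = 0.0798. Chance imbalance in position adds (0.28 × *s*/2)². I assume the same imbalance and a linear spread of the same size for version.
- *s* = 0.3: 0.042² = 0.0018, or 2.2% each and 4.4% for both.
- *s* = 0.5: 0.070² = 0.0049, or 6.1% each and 12.3% for both.

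Adding the terms costs up to about 2%. The unadjusted variance relative to the adjusted one is therefore 1.044/1.02 = 1.02 and 1.123/1.02 = 1.10. With no effects it is 1/1.02 = 0.98, a small loss from adjusting.

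**4. Power for group by time.** Simulation with 60 and 43 participants and an interaction of 0.45 × √2 = 0.64 residual SD for 60 vs 40 minutes. There were 3,000 runs, so the Monte Carlo SE is about 0.9 points.

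| Position/version effect (SD) | Without terms | With terms |
|---|---|---|
| 0/0 | 60.9% | 60.1% |
| 0.3/0.3 | 57.1% | 58.5% |
| 0.5/0.5 | 57.0% | 60.8% |
| 1.0/0.5 | 49.6% | 59.9% |

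The mean estimate is unbiased either way, and type I error without the terms is 4.6 to 5.0%.

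**5. If balance was held within group.** At effects of 0.3 to 0.5 SD the estimate's variance falls by only about 1 to 3% when the terms are added. Position and version variance still inflates the model's standard error. At 1.0/0.5 SD, type I error without the terms falls to 2.6%, and power is 49.5% without them against 60.5% with them.

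**6. What the pilot can exclude.**
- *Version.* For n = 30 the Wilcoxon mean is 30 × 31/4 = 232.5 and the SD is √(30 × 31 × 61/24) = 48.62. A vs B (V = 145): z = −1.80, P = .072, matching the printed .07; r = 1.80/√30 = 0.33, with rough 95% limits 0.33 ± 1.96/√30, or −0.03 to 0.69. B vs C (V = 310): z = 1.59, r = 0.29.
- *Order.* t/√30 gives 0.04, −0.03 and −0.07. With half-width 2.045/√30 = 0.37, the limits reach at most −0.45 and 0.41.
- *Power.* Thirty students give 80% power only for a paired *d* of about 0.53, or about 0.62 with Bonferroni adjustment over three tests.

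**The case against.** Several objections are sound and limit the point.

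- **The quoted claim concerns systematic influence.** In that sense it is right: the estimates are unbiased over randomisations. This stands.
- **Non-attendance.** A reader might infer that losing 42% of those assigned biases the comparison. The document does not support that. Ethical Considerations restricts the sequence files until the session, so absence should not depend on sequence, and Participant Flow does not say that every absentee already had one.
- **Balance within group.** A reader might infer that counterbalancing ignored group. The text is silent on this, and Figures 1 and 2 are not shown.
- **Version is not ignored.** IRT equating is the stated handling of version difficulty, and the Discussion credits equivalence to the IRT design. The Pilot Study section itself claims only an absence of significant differences.
- **Fatigue is not shown.** The pilot order contrasts were near zero (global P = .90). Greater fatigue in ADHD is conjecture, because no pilot result is given by diagnosis.
- **The index is loose.** The 0.33 is z/√n, an r-type quantity, and cannot be set directly against the design *d* of 0.45.
- **The model may be abbreviated.** The mixed model's fixed effects are not fully listed, so a position term is not expressly excluded. However, the ANOVA is stated with time as its factor, and the contrasts and Welch tests are given without adjustment. The section fixes the degrees-of-freedom method, the likelihood ratio check and the packages, while Intervention Procedures relies on counterbalancing for order. That is enough to raise the point.

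**Conclusion.** The point holds as a matter of efficiency and clear specification. Position and version are randomised and recorded, no stated performance analysis names them, and exact balance is arithmetically impossible overall and among controls. For effects of up to 0.5 residual SD, leaving them out makes the group-by-time variance roughly 0 to 10% larger if sequences were pooled across groups. If balance was held within group, the estimate's variance changes little, but a large position effect would make the test conservative. The gain in power is about 1 to 4 points at 0.3 to 0.5 SD and about 10 points at 1.0/0.5 SD; with no effects it is a loss of about 1 point.

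All these sizes rest on assumed effects, because the document gives none, and on attendance unrelated to sequence. The pilot leaves version differences of moderate size open and makes large order effects less likely, so the lower part of the range is the more plausible for position. No bias and no inflated type I error is claimed.

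**What to change.** 1. Add fixed effects for position (1 to 3) and version (A to C) to the mixed model, with group × position as a sensitivity analysis.
2. Take the time contrasts and the group-by-time contrasts from that model.
3. State whether sequences were balanced within ADHD and control, and report attained position and version balance by group among attendees.
4. Report version differences with 95% CIs rather than resting on non-significance.
5. Because analysis began in March 2026, date the change and say whether group-by-time results had been seen.

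**Cost.** Four model degrees of freedom, or six with group × position, out of 103 × (3 − 1) = 206 within-person degrees of freedom. No data are needed beyond the allocation file. If the effects are nil, the variance of the interaction estimate rises by about 1 to 2%.
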